### Setting and recruitment

To assess the potential of SMART to promote behavior change in people with epilepsy and NHEs, the investigators will build on their strong track record of working with local federal, state, and county entities that provide service to rural and underserved communities. At the Iowa site, study participants will be drawn from local clinical and community referral sources including the Epilepsy Foundation of Iowa and primary care networks. At the Ohio site, enrollment will emphasize recruitment outside of the Cleveland metropolitan area with assistance from the Epilepsy Association, Epilepsy Alliance of Ohio, and epilepsy care professionals affiliated with the University of Cincinnati. This will include advertisements and brochures. We will also obtain HIPAA Waivers of Authorization from the relevant IRBs at the recruiting sites so that we may identify and contact potential subjects. Since SMART is an adjunct to ongoing neurological and medical care, it is expected that study participants will continue to receive services with their regular medical clinicians and providers at all sites.

Participants will have a self-reported diagnosis of epilepsy, be at least 18 years of age, have experienced an NHE within the last 6 months, and be able to provide written informed consent and participate in study procedures. Study entry criteria are purposely broad in order to best represent “real world” people with epilepsy [15]. Actively suicidal/homicidal individuals and those with dementia will be excluded, as will pregnant women who are likely to need different and more intensive treatments.

The study team will attempt to oversample PLWE who live in rural or semi-rural settings. Classification of rurality will be determined based upon the 2013 Rural-Urban Continuum Codes [16], a classification scheme that distinguishes metropolitan counties by the population size of their metro area and nonmetropolitan counties by degree of urbanization and adjacency to a metro area. The official Office of Management and Budget metro and non-metro categories have been subdivided into 3 metro and 6 non-metro categories. Each county in the USA is assigned 1 of the 9 codes.

In addition to the RCT participants, the investigators will enroll and train up to 8 peer educators using procedures like those conducted in previous work [17]. A peer educator will be an individual with epilepsy who has had at least 3 previous lifetime NHEs. Informed consent will be obtained for all focus group members, peer educators, and RCT participants, by study staff during the enrollment process. Additional consent must be obtained to include the de-identified subject data in the MEW network database. All work will be conducted consistent with Institutional Review Board (IRB) approval at the relevant sites. Adverse events will be reported to the IRB. Regular meetings between the enrolling sites will communicate any changes in protocol. Annual updates will be provided to the CDC, including any adverse events. This is a low-risk study, but if a participant is identified as suicidal or homicidal during the screening process or at any time during the study, the study staff interacting with the individual will use existing clinical infrastructure to insure safety and appropriate clinical follow-up. The primary investigators will monitor the study to ensure data integrity and the safety of the participants at weekly meetings with study staff. The study biostatistician will review the data for discrepancies after about one-third of participants have been enrolled, at the midpoint of enrollment, and on completion of enrollment. The study data coordinator, who will not be involved in the study intervention and has no contact with participants, will review the study records for compliance with IRB requirements and verification of source documents.

Confidentiality of the research data will be protected in several ways. Paper assessment forms and other study records will be stored in locked research offices. Subjects will be identified by a separate study ID number on all study records. The lists that link study ID codes with subject names and all study records will be stored on password-protected, encrypted computers or secure servers. Only aggregate data will be presented or published and will be presented such that individual patients cannot be identified. Study personnel sign a pledge of confidentiality as a requirement for employment. All study personnel will be required to be certified in the protection of human subjects throughout the study.

Retention efforts will also be maximized by using known strategies to increase retention, including providing participants with a copy of their study visit schedule including a list of procedures to be completed at each visit, e-mail and telephone visit reminders, and keeping multiple updated forms of contact. Participants who do not participate in a SMART session or a research assessment will be called the same day to have the appointment rescheduled. If problems with adherence arise, we will explore with the participant the potential obstacles and ways to improve adherence. After the first year of the project, CAB meetings will be held annually to review study progress and suggest additional strategies that might be needed should recruitment or enrollment be less than expected targets.

Upon project completion, the investigators will present findings to the UI Prevention Research Center, our project-specific CAB, and the CDC MEW Network Coordinating and Collaborating Centers and to community health partners. Findings will be presented at relevant scientific venues and in peer-reviewed publications and may help to scale-up epilepsy self-management program opportunities. We will contribute our de-identified data to the MEW Network database so that it can be shared with a larger audience of scientists interested in epilepsy self-management. Individuals outside of the MEW Network have the opportunity to access MEW data, under appropriate data-sharing agreements, by presenting an analysis proposal to the MEW Database Steering Committee. In addition to the above, we will also post study results on www.clinicaltrials.gov and will make de-identified data available to other qualified investigators in the research community. In all cases, data will be shared as soon as it is available and for as long as the format allows.

### Experimental intervention

The SMART curriculum is divided into 2 steps. Step 1 consists of eight group format 45–60-min sessions with up to 10 participants per group, which will be collaboratively delivered by a nurse educator and a peer educator. The intervention will be delivered in a Web-based format emphasizing interactive discussion with a secure videoconferencing system. Participants will be able to log on and interact via audio and/or video. Telephone call-in will be available for those who do not have Internet access. Patients will receive e-mail and phone call reminders of sessions, and make-up sessions will be available. The initial group-session portion of SMART will be completed over 10–12 weeks (Table 1). Following the step 1 group sessions, step 2 consists of 3 brief (no more than 15 min) monthly Web-based or telephone maintenance sessions conducted by the nurse educator. Telephone sessions will address ongoing issues of epilepsy self-management including treatment adherence. Additionally, the nurse will serve as a facilitator of linkage between the individual’s epilepsy care clinicians by providing SMART program status updates to providers.

**Table 1 Tab1:**
[figure not shown]
SMART curriculum: topics covered in each session

### Waitlist (WL) control

Individuals randomized to WL will continue in their usual care. After they complete their 13-week and 6-month assessments, which are identical to the SMART group assessments, WL individuals will begin participating in the SMART intervention for the next 12 weeks. Once the WL individuals begin participating in SMART, they will have research assessments at 13 weeks, 6 months, and 12 months after beginning SMART.

### Feasibility and fidelity

Attendance for each SMART session will be recorded. Acceptability will be assessed at the end of each 12-session group series with a brief self-rated survey. Following Fraser [18], fidelity to the SMART intervention will be assessed quantitatively and qualitatively. Non-interventionist research staff will monitor and assess at least 25% of group sessions, with each fidelity dimension being rated on a 1–10 scale.

### Outcomes and analysis

Table 2 outlines study procedures. In addition to demographic and clinical information (age, gender, ethnicity, self-reported cumulative medical illness [19, 20]), health literacy will be assessed [21] to detect persons with limited or marginal health literacy. For both the SMART and the WL groups, research assessments will be done at screening (to establish study eligibility), at baseline, and at 13 weeks, 6 months, 12 months, and 18 months after randomization. Members of the waitlist will also be assessed 13 weeks after starting the SMART intervention. All assessments are suitable for remote administration either by phone or using REDCap (Research Electronic Data Capture), a secure Web application for building and managing online surveys and databases [22]. REDCap will be used for secure data entry and storage.

**Table 2 Tab2:**
[figure not shown]
Phase 2/RCT procedure. *Wk* week, *Mth* month, *NHE* negative health events, *EOS* end of the study

#### Primary outcome

The primary outcome will be the proportion of individuals with reduction in their total number of NHEs in the prior 6 months at baseline compared to week 24 of the trial. The prior SMART study had a nonstandard distribution of NHEs and a high proportion of subjects with no NHEs at 6-month follow-up, so a longitudinal binary mixed model (no NHE or at least one NHE) will be used as opposed to a count regression model [10]. The second primary outcome will be the change in NHE counts in the 6 months prior to baseline compared to week 24 of the trial. NHEs are defined as seizures, emergency department visits, hospitalizations, and self-harm attempts. NHE reporting will be via self-report with corroboration by EHR documentation and report of family/support system informants whenever possible. In addition to total NHEs, we will assess NHEs in each category, including seizure frequency and length of stay in days for hospitalization NHEs. These domains (total number of NHEs, seizure frequency, length of hospital stay) will be assessed for differences between the two groups looking at mean and median values. A type I error rate of 0.05 will be considered significant.

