The 12-month and 18-month measurements of NHEs will be compared to baseline and 6-month measurements as well. We will also examine change-over-time in the secondary outcomes using parametric and/or non-parametric tests as deemed appropriate for each measure. NHE measurements will reflect the preceding 6-month time period, except for the 13-week time period. The 13-week NHE measurement will reflect the time period following baseline (when individuals participating in SMART will be having their “intensive” group sessions), and it will be used to assess for within-subject differences from baseline to 13-week and 13-week to 6-month time periods. Note that the 13-week to 6-month NHE count will be derived by subtracting the measurement taken at 13 weeks from the one taken at 6 months. This will allow for a greater understanding of the time course for when the expected reductions occur in the SMART group, which we expect to mostly occur after the “intensive” 8 group sessions have ended. A secondary analysis of NHEs will include a comparison of hospital and emergency department visits. A 2-sided type I error rate of 5% will be considered significant.

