### Sample size calculations

Psychosocial interventions can reduce seizures and emergency department visits in people with poorly controlled epilepsy [34, 35]. Oosterhuis noted a 50% reduction in seizures with group psychoeducation [36]. In our original SMART efficacy trial, a total number of past 6-month NHEs were reduced by > 50%. The projected sample size is 160, with 80 subjects per arm. While the Web and phone-based access format of SMART optimized study retention and attrition rate in the original RCT was 14.2%, we conservatively assume 20% attrition at 6 months (*N* = 128). A 2-sided, 2-sample, Fisher’s exact test with a type I error of 5% will have 86% power to replicate the difference in the proportion of individuals with NHE reductions. For the second primary outcome which has a Laplace distribution, a 2-sided, 2-sample, Wilcoxon-Mann-Whitney test with a type I error of 5% will have 89% power to replicate the difference in NHE counts in the prior 6 months.

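### The article is inconsistent on whether it has one or two primary outcomes, each of the two is given a full 5%, and nothing says which result makes the trial positive

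*Protocol article*

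**What the plan says.** Four places in the protocol article bear on this.

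- **Primary outcome.** Two outcomes carry the label. The first: "The primary outcome will be the proportion of individuals with reduction in their total number of NHEs in the prior 6 months at baseline", set against week 24. The second: "The second primary outcome will be the change in NHE counts in the 6 months prior to baseline compared to week 24 of the trial". One unsplit level follows: "A type I error rate of 0.05 will be considered significant".
- **Sample size calculations.** Each outcome has its own power statement at the full level. For the proportion, the claim reads "exact test with a type I error of 5% will have 86% power to replicate the difference in the proportion of individuals with NHE reductions" (Fisher's test). For the count, introduced by "For the second primary outcome which has a Laplace distribution", the statement is "a 2-sided, 2-sample, Wilcoxon-Mann-Whitney test with a type I error of 5% will have 89% power".
- **Data analysis.** Only the proportion is called primary here. The Wilcoxon-Mann-Whitney test of counts follows as an additional test without that label. The section closes with "A 2-sided type I error rate of 5% will be considered significant".
- **Abstract, Methods.** A single primary outcome is named, changes in NHEs, without saying whether as a proportion or a count.

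None of these gives a testing order, a split of the 5%, or a statement that one, either or both results must be significant.

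**The concern.** This is a replication trial, so a reader needs to know in advance what counts as having replicated. The two tests use the same NHE change score but are not identical, so one can be significant when the other is not. The article does not say what would be concluded then.

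The choice of rule has consequences. If either outcome is enough, two tests at 5% give more than a 5% chance of at least one false positive. If both are needed, the power of the trial is neither 86% nor 89% but their joint probability. If the 5% were split, neither stated power would apply. If only the proportion decides, there is no multiplicity problem, but the count outcome should not then be called primary.

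**Working it through.** **Inputs from the article.** 160 randomised 1:1, 20% attrition, two-sided 5% for each test, power 86% (Fisher) and 89% (Wilcoxon-Mann-Whitney).

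**The plan's own figures.** 160 × (1 − 0.20) = 128, or 64 per arm, which agrees with the article. The two powers cannot be reproduced, because the article gives no responder proportions and no Laplace location or scale. As a guide, exact enumeration of Fisher's test at 64 per arm needs a difference of about 24 to 28 percentage points for 86% power, for assumed control rates of 20% to 65%. The 86% and 89% are taken as given below.

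**Rule A: either outcome suffices.**

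- Bound under any dependence: 0.05 + 0.05 = 10%.
- Value if the tests were independent: 1 − 0.95² = 9.75%. They are not independent, since both use the same change score.
- Exact size of Fisher's test at 64 per arm, for assumed common response rates of 20% to 65%: 3.0% to 3.5%. With that size, the sum bound falls to about 3.5% + 5% = 8.5%.
- Simulated null, 40,000 trials per scenario, 64 per arm, both tests on the same change scores. The distributions are assumptions:

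| Assumed change score | Fisher | Wilcoxon | Either | Both |
|---|---|---|---|---|
| Laplace, median 0 | 3.08% | 4.97% | 6.15% | 1.91% |
| Laplace, median −0.5, scale 1 | 3.00% | 4.85% | 6.28% | 1.56% |
| Rounded Laplace, −1, scale 3 | 3.48% | 4.92% | 6.36% | 2.05% |
| Rounded Laplace, −2, scale 10 | 3.40% | 4.93% | 6.31% | 2.02% |
| Overdispersed count change | 3.31% | 4.86% | 6.07% | 2.10% |

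The columns agree with either = Fisher + Wilcoxon − both; for example 3.31 + 4.86 − 2.10 = 6.07. The either-wins rate is 6.1% to 6.4% here. Smaller runs under other assumed distributions ranged from 5.6% to 7.4%.

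**Rule B: both outcomes required.** The overall error is at or below 5%. Joint power lies between 0.86 + 0.89 − 1 = 75% and min(0.86, 0.89) = 86%. Independence would give 0.86 × 0.89 = 76.5%. Positive correlation moves the value up towards 86%.

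**Rule C: Bonferroni, 0.025 each.** By normal approximation, new power = Φ(z_power + 1.960 − 2.241).

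- Fisher: Φ(1.080 + 1.960 − 2.241) = Φ(0.799) = 78.8%. Exact enumeration gives 77.8% to 79.7% for the assumed control rates.
- Wilcoxon: Φ(1.227 + 1.960 − 2.241) = Φ(0.946) = 82.8%.

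**Rule D: fixed sequence, proportion first.** If the null hypothesis for the proportion is true, any false claim requires that test to reject, with probability at most 5%. If it is false, the only possible false claim is on the count, again tested at 5%. The overall error is therefore at or below 5%, and the 86% is unchanged. The count outcome is confirmed only when both tests reject, so its power is the joint value of Rule B, 75% to 86%, not 89%.

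**The case against.** The strongest reply is that a multiplicity rule commonly sits in the statistical analysis plan or full protocol, neither of which is shown, so its absence from an article is no fault. That is right as far as it goes. The per-test powers are also compatible with a fixed sequence or a both-required rule, since each tests both outcomes at 0.05; only a split of alpha would contradict them. What the reply does not remove is the contradiction inside this document: two sections give the count outcome primary status and the other two do not. A separate plan cannot make those sections agree.

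A second reply is that the excess error is small. That stands: it is roughly one to one and a half points in the main simulations, and only under Rule A.

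A reader might infer more than the documents support:

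- **That the false-positive rate does exceed a stated trial-wide 5%.** The 5% is worded as a significance level for tests, not as a trial-wide rate, and no section adopts an either-wins rule. If the proportion alone decides, or both are required, the rate stays at or below 5%.
- **That the inflation is close to 10%.** The 9.75% figure requires independence and 10% is only a bound. Adding the model of any versus no NHE would raise the rate, but the Data analysis section labels that model exploratory.
- **That the comparisons by NHE category, or of means and medians, are further primary tests.** They share the section and its 0.05 sentence, but are never called primary.

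**Conclusion.** The point holds in a conditional and modest form. The article fixes its success criterion inconsistently: two primary outcomes in the Primary outcome and Sample size calculations sections, one in the Abstract and Data analysis sections, and no statement of which result makes the trial positive. An excess of false positives is not demonstrated; it arises only if a win on either outcome counts. It is then about 6% instead of 5%, assuming 64 evaluable per arm and the distributions listed. If both must win, the cost is in power: at most 86% and possibly as low as 75%, taking the article's two figures as correct. The ambiguity itself matters more than the size of the inflation, because it leaves open which result would be claimed if the two tests disagree.

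**What to change.** State a fixed sequence in the order already listed, before outcome data are seen: the proportion with an NHE reduction by Fisher's exact test at two-sided 0.05, then the change in NHE count by the Wilcoxon-Mann-Whitney test at two-sided 0.05 only if the first is significant. Align the Abstract, Primary outcome, Data analysis and Sample size calculations sections with it. As a minor clarification, label the per-category and mean/median comparisons as secondary or descriptive.

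The cost is a sentence or two and no change to the 160. The count outcome cannot be claimed as confirmatory if the first test fails, and the 89% should be described as the power of that test taken alone.

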#### Secondary/additional outcomes

Additional assessments will include evaluation of depressive symptoms using the PHQ-9, a widely used and validated self-rated depression scale [23]. Functional health status will be assessed using the 36-Item Short Form Survey (SF-36), a multi-purpose, short-form health survey that yields two psychometrically based components: a physical component summary and a mental component summary, which has proven useful for comparing the relative burden of diseases [24]. Epilepsy control will be assessed via self-reported seizure frequency. Quality of life will be assessed with the Quality of Life in Epilepsy (QOLIE-31) self-administered questionnaire which comprises 7 components including seizure worry, overall quality of life, emotional well-being, energy-fatigue, cognitive functioning, medication effect, and social function [25, 26]. These domains (score on PHQ-9, score on SF-36, self-reported seizure frequency, and score on QOLIE-31) will be assessed for differences between the two groups looking at mean and median values at baseline and 13 and 24 weeks of trial and change over time from baseline to 24 weeks of trial. A type I error rate of 0.05 will be considered significant.

Other factors assessed in the trial include epilepsy self-management competency, self-efficacy, social support, and stigma. Self-efficacy will be measured with an Epilepsy Self-Efficacy Scale (ESES) 2000 version. The ESES was developed based on Bandura’s conceptualization of self-efficacy to assess a person’s confidence in his or her ability to use self-management strategies. Previous studies show acceptable construct validity and high test-retest reliability in the ESES [27–29]. Social support will be measured with the Multidimensional Scale of Perceived Social Support (MSPSS), a 12-item scale that measures an individual’s perception of social support provided by family and friends, as well as satisfaction with that support [30]. Stigma for epilepsy will be measured using the 24-item Stigma Scale of Epilepsy (SSE) developed by the Demonstration Project on Epilepsy as part of the WHO/ILAE/IBE Global Campaign against Epilepsy [31, 32]. The SSE is a validated, versatile, and sensitive instrument which has been used mainly in resource-poor settings to study stigma in epilepsy.

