A new SMART 2.0 research study is intended to (1) replicate efficacy findings of the original SMART randomized control trial (RCT) in an alternative setting (rural and semi-rural communities), (2) incorporate best practices and recommended strategies for enhancing study recruitment and retention, and (3) assess program adopter’s perceptions of the intervention to inform future implementation and dissemination. This report describes the methods of the planned replication study using a prospective 2-site, 6-month RCT design to assess SMART vs. 6-month waitlist (WL) control. The study will assess effects on epilepsy complications and other outcomes in a diverse sample with epilepsy including rural people with epilepsy. We hypothesize that at 6-month follow-up, SMART will be associated with reduced negative health events (NHEs) compared to WL. We also expect that SMART will be associated with improved quality of life, functioning, and physical and mental health.

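### Four secondary domains are judged at an unadjusted 0.05 over several contrasts, with no main contrast, no fixed test and no supportive label, so the chance of a false significant result is well above 5%

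*Protocol article*

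**What the plan says.** The Secondary/additional outcomes section lists four domains: "These domains (score on PHQ-9, score on SF-36, self-reported seizure frequency, and score on QOLIE-31". It describes the SF-36 as giving two scores, "a physical component summary and a mental component summary", so the four domains supply four or five scores. These domains "will be assessed for differences between the two groups looking at mean and median values at baseline and 13 and 24 weeks of trial", with a further contrast, "change over time from baseline to 24 weeks of trial". The sentence that follows is "A type I error rate of 0.05 will be considered significant".

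The Data analysis section adds: "We will also examine change-over-time in the secondary outcomes using parametric and/or non-parametric tests as deemed appropriate for each measure". It ends with "A 2-sided type I error rate of 5% will be considered significant".

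The Background section attaches a directional expectation to the same areas: "We also expect that SMART will be associated with improved quality of life, functioning, and physical and mental health".

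The word exploratory is used once in the analysis text, for the longitudinal mixed models of negative health events (NHEs). It is not used for the secondary domains. Self-management competency, self-efficacy, social support and stigma come after the 0.05 sentence, and no error rate or between-arm test is stated with them.

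**The concern.** Each domain can be called significant on a 13-week difference, a 24-week difference or a change to 24 weeks, by whichever test is judged suitable. Nothing in the article says which of these decides, or that the results are only supportive. When several correlated chances at 0.05 share no common rule, the error rate over the set exceeds 5%.

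This matters for how the trial is reported. The Phase 2 section says that participants and educators are not blinded, and these domains are self-reported. They are therefore a likely place for a favourable-looking difference. If the NHE outcomes were negative, a single p-value below 0.05 on one scale at one visit could receive more weight than it deserves.

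**Working it through.** The article states a per-test rate of 0.05 and no rate for the set, so there is no plan figure to reproduce.

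**Inputs from the article**
- Error rate per test: 0.05, two-sided (Secondary/additional outcomes; Data analysis). The nominal rate in the benefit direction is 0.05 / 2 = 2.5%.
- Scores: 4, or 5 if the SF-36 gives its two summaries.
- Post-baseline contrasts: 13 weeks, 24 weeks, change to 24 weeks. Baseline comparisons are left out because they cannot show a treatment benefit.
- Evaluable participants: 160 × 0.80 = 128, or 64 per arm (Sample size calculations).

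**Assumptions not in the article**
- Correlation between scores 0.3 to 0.7; correlation between visits 0.6.
- Normally distributed scores.
- The second test, if used, is the Wilcoxon-Mann-Whitney test, the only rank test the article names.

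**Step 1: independent tests.** The chance of at least one false positive in k tests is 1 − 0.95^k in either direction and 1 − 0.975^k in the benefit direction.
- k = 4: 18.5% and 9.6%
- k = 5: 22.6% and 11.9%
- k = 12 (4 scores × 3 contrasts): 46.0% and 26.2%
- k = 15 (5 scores × 3 contrasts): 53.7% and 31.6%

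These figures are too high for this trial, because the scores, the visits and two tests on the same data are all correlated.

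**Step 2: simulation with dependence.** Trials were simulated with no treatment effect and 64 per arm. The ranges cover 4 and 5 scores and the between-score correlations above.

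| Reading of the plan | Any p < 0.05, either direction | False benefit |
|---|---|---|
| One test of change per score | 12-21% | 6-11% |
| 13 weeks, 24 weeks and change, one test each | 29-47% | 15-25% |
| The same three contrasts, t-test and Wilcoxon test | 34-53% | 17-28% |

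A repeat run with the same settings moved the ends of these ranges by no more than about three percentage points.

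**Step 3: comparison with the nominal rates.** On the most lenient reading, the either-direction rate is 12/5 = 2.4 to 21/5 = 4.2 times 5%. The false-benefit rate is 6/2.5 = 2.4 to 11/2.5 = 4.4 times 2.5%. The excess therefore does not depend on counting every contrast or on doubling the tests.

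**The case against.** The strongest reply is that these outcomes are plainly secondary. The section heading calls them secondary or additional, power is calculated only for the two NHE outcomes, and the Background section hypothesises about NHEs but only expects benefit elsewhere. Unadjusted secondary outcomes read as supportive are common practice. A condensed article may also leave their ordering and the exact tests to an analysis plan that is not shown.

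Much of this stands. The absence of a hierarchy would not be a point in itself, and statisticians differ on whether secondary outcomes need one. What remains is that the article does not stay silent: it states the significance rule and attaches it to a list of contrasts without saying that the results are supportive.

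The phrase about means and medians may describe summaries, with one test then chosen per measure. The Primary outcome section uses similar wording for NHE domains, while the Data analysis section gives the change in NHE counts a single test. That reading is fair, and the one-test rows of the table apply to it.

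A reader might infer more than the text supports:
- **That a false benefit is likely, or occurs more often than not.** It does not: the false-benefit rate is at most about 28% here, and the higher figures include differences in the harmful direction.
- **That the overall rate is about 60%.** This needs a median test that the article never names.
- **That all secondary measures are affected.** The 0.05 sentence does not cover self-efficacy, social support, stigma or competency.
- **That a secondary result could count as replication if the NHE outcomes fail.** The Sample size calculations section ties replication to the NHE outcomes.
- **That any baseline difference can only be chance.** The Data analysis section says that baseline assessment follows randomisation after a delay, so this is too strong. Baseline tests are not in the figures above.

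**Conclusion.** The point holds for the four named domains. With an unadjusted 0.05, several contrasts and an open choice of test, the chance of at least one false significant difference is about 12-21% on the narrowest reading and 34-53% on the broadest. For a false benefit it is about 6-11% and 17-28%. The sizes rest on assumed correlations, normal scores and 64 per arm. The direction of the result does not depend on them: even the lowest value is more than twice the nominal rate. The primary conclusion is untouched. This is a moderate point about which secondary results may be called significant, and it should be corrected in the wording.

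**What to change.** In the Secondary/additional outcomes section:
- Name one contrast per domain, change from baseline to 24 weeks, with one stated test, and say whether the SF-36 contributes one or two scores. Align the open test choice in the Data analysis section with this.
- Label the 13-week contrasts, the cross-sectional 24-week contrasts and any second test as supportive or exploratory. Report them as estimates with 95% confidence intervals and no statement of significance.
- State that the four domains are supportive and not adjusted for multiplicity. If they are to carry significance claims, use Holm or a fixed order instead. As an illustration of scale, Bonferroni over four domains with one test each would be 0.05 / 4 = 0.0125 per test.
- Report baseline values by arm descriptively.

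This needs no extra data or participants. The cost is that fewer secondary results can be called significant.
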